**Table 1:**

**Schedule of Visits and Assessments**

| **Visit** | 0  Screening  Phase | 1  Baseline | 2 | 3 | 4 | 5 | 6 | 7 | 8 | 9 |
| --- | --- | --- | --- | --- | --- | --- | --- | --- | --- | --- |
| **WEEK** |  | 0 | 1 | 2 | 3 | 4 | 5 | 6 | 7 | 8 |
| **SCREENING AND CONSENT** |  |  |  |  |  |  |  |  |  |  |
| Informed consent | x |  |  |  |  |  |  |  |  |  |
| Ongoing capacity | x |  |  |  |  |  |  |  |  |  |
| Inclusion / exclusion criteria | x |  |  |  |  |  |  |  |  |  |
| Baseline demographics | x |  |  |  |  |  |  |  |  |  |
| **SAFETY** |  |  |  |  |  |  |  |  |  |  |
| Adverse events (before/after each session by the AEP) |  |  | x | x | x | x | x | x | x | x |
| **EFFICACY** |  |  |  |  |  |  |  |  |  |  |
| Accelerometry (worn for 5 days prior to randomisation) |  | x |  |  |  |  |  |  |  |  |
| SIMPAQ |  | x |  |  |  |  |  |  |  |  |
| Preferences, Barriers, Motivators Questionnaire |  | x |  |  |  |  |  |  |  |  |
| WHO DASS 2.0 |  | x |  |  |  |  |  |  |  | x |
| BPRS |  | x |  |  |  |  |  |  |  | x |
| SANS |  | x |  |  |  |  |  |  |  | x |
| BREQ 3 |  | x |  |  |  |  |  |  |  | x |
| Physical Capacity (6MWT, 30 sec sit-to-stand, grip strength, push up test) |  | x |  |  |  |  |  |  |  | x |
| Physical Health measures (BP, height, weight, waist circumference) |  | x |  |  |  |  |  |  |  | x |
| 12RM strength, chest press and squat(RT only) |  | x |  |  |  |  |  |  |  | x |
| SEES |  |  |  |  | x |  |  |  |  | x |
| **INTERVENTION SESSIONS** |  |  |  |  |  |  |  |  |  |  |
| RT and AIT (x3 sessions per week) |  |  | x | x | x | x | x | x | x | x |
| Health Coaching Sessions offered |  |  | x |  | x |  | x |  | x |  |
| **ACCEPTABILITY** |  |  |  |  |  |  |  |  |  |  |
| Acceptability questionnaire |  |  |  |  |  |  |  |  |  | x |
|  |  |  |  |  |  |  |  |  |  |  |
| Individual interview (RT condition) - optional |  |  |  |  |  |  |  |  |  | x |

## Study Restrictions

For the period of this study, participants will be asked not to engage in exercise outside of the exercise type they have been randomised to, outside of supervised study sessions.

**Safety Assessments**

All patients recruited in this study will be active cases at Metro South Addiction and Mental Health Service Community Care Units. The study team will liaise with clinical staff to ensure that there are no unforeseen contraindications to the participant being involved.

Both resistance training and aerobic interval training are considered safe and feasible for people with severe mental illness, and all sessions will be fully supervised by an AEP (7, 8).

### Adverse Events

Data on adverse events in both conditions will be reported, including any new injuries, exacerbations of pre-existing conditions, participant withdrawal and reasons and adverse events judged to be as a direct result of the intervention will be specifically recorded in the case report form. We will examine adverse events at before and after each training session. All adverse events reported between consent and final visit will be recorded in the case report form (CRF). The investigator or AEP will ask the Participant non-leading questions in an effort to detect adverse events e.g. “How have you been over since the last session”. We expect that adverse events will occur during the study related to fluctuations in the underlying mental disorder and medications and adjustment to increased physical activity.

# Investigational Exercise(s)

## Description of Investigational Exercise(s)

The study will be conducted onsite at each CCU, within the shared courtyard, using pre-existing gym facilities and equipment maintained by each CCU. Both resistance training and AIT will be conducted in accordance with recommendations from the Sports Science Checklist (Supplementary material 1), in order to improve both the quality of reporting, and of methodological aspects of training and fitness assessments.

Both conditions will offer engagement in a total volume of moderate intensity exercise that will be greater than 90 min per week, which has been shown to be associated with improvements in mental health outcomes (13). Both exercise conditions (RT and control) will be aimed at moderate intensity exercise that will be balanced for total number of sessions and volume. The total volume of activity in RT was estimated to match what would have been attained if assigned to the AIT and in line with previous research protocols comparing aerobic with RT interventions in this population.

**7.1.1 Resistance training Intervention (RT)**

The World Health Organisation and Australian Physical Activity Recommendations suggest resistance training to occur on 2 or more days per week, involving main muscle groups (9, 10).

The intervention will involve resistance training three days per week, using a variety of resistance training equipment such as hand weights and resistance bands appropriate for small clinical gym settings to enable replication of the study without substantial investment in specialised equipment or gym spaces.

There will be a 10 minute stretching warm up and 5 minute cool down. The resistance training intervention will take approximately 30 minutes duration, with total duration 45 minutes. The active exercise volume will be progressed to 40 minutes by week 4 of the intervention, with a total duration of exercise being 50-55 minutes.

Resistance training will be progressive and tailored to the individual participant’s current ability/ exercise capacity and exercise history via individually prescribed programs, taking into account participants with schizophrenia who may be deconditioned and may have little experience with resistance training. At all times training will be tailored to their experience level by experienced AEP’s trained exercise prescription. An initial assessment of muscle strength will be assessed using the 12 repetition maximum test (12-RM) for relevant large muscle groups to guide exercise prescription, which is an appropriate proxy measure to estimate the 1-RM (1 Repetition Maximal test) in poorly conditioned individuals, using an established conversion formula; Brzycki 1RM Formula, 1RM = Weight x (36 / (37 – Repetitions),(11).

The aim will be to increase muscle strength progressively over the 8 weeks. Training will be appropriate for beginners and be aimed at moderate intensity (40-70%) of estimated maximum strength, (1-RM). Week 1 will start with 40% of 1-RM, and progressed with 5% increments each week as per capacity of the individual, with 3 sets of 8-10 repetitions, of approximate 40 seconds duration per set, and a 90 seconds duration between sets.

Six exercises across main muscle groups used in activities of daily living will be prescribed per resistance training session. As strength increases, sessions will be progressed using heavier weights, however each participant will be monitored for their response to training, and progression individualised. A typical session will include 6 exercises that target main muscle groups such as lower legs, back, arms/shoulders, and core, using a variety of standard resistance training equipment, for example; hand weights, kettle bells, resistance bands and a chest press bar and floor mat. Exercises will include Romanian and sumo squats, forward lunges, bicep curls, tricep extensions, calf raises, reverse fly, shoulder press and crunches. All exercises are appropriate for resistance training in untrained participants and will be supervised by the AEP employed at each site. The content and weights of each session will be recorded using standard protocol.

**7.1.2 Aerobic Interval Training (AIT)**

Participants randomised to the aerobic interval intervention will engage in a 10 minute warm up and 5 minute cool down and a 30 minute aerobic interval training intervention in a circuit style, with total duration of exercise 45 minutes. The active exercise volume will be progressed to 40 minutes by week 4 of the intervention, with a total duration of exercise being 50-55 minutes.

Equipment used for the circuit will include a stationary bike, a treadmill, boxing pads and gloves, step and mat. The circuit stations will vary each week to reduce boredom. Stations are designed such that they could be modified (regressed/progressed) to suit individual participant capacity and preference.

Participants will engage in a circuit style training supervised by the AEP at each site, three times per week. The aerobic intervention will begin slowly, aimed at beginners, but adapted for experience level and baseline fitness of participants.

Intensity of the aerobic intervention will be monitored using the Borg Category Ratio 10 scale of Perceived Exertion scale (RPE) (24), a 10 point scale to assess subjective perception of effort that has been calibrated against exercise intensity and will guide intensity of exercise prescription. Initial prescription will be aimed at an intensity achievable for participants with low initial CRF but progressed to reach moderate intensity by week 3 (12). The AEP will aim for the participant to maintain an RPE at 2–3 for the first 2 weeks, then increased to a minimum RPE of 4/10 by week 3 and further increased by 5% each week as per individual participant's capacity. Following warm-up, participants will rotate through interval stations, beginning with four minutes of exercise interspersed with three minutes of active recovery (reduced intensity interval RPE 1-2) until a total of 30 minutes of MIIT is completed. Participants will progress to five minute active intervals as the participants' functional capacity increases.

**7.1.3 Fidelity**

A one day training program for AEP’s at each CCU will be conducted in order to train them in the specific delivery of the intervention such that participant programs will be standardised for each condition and conducted in accordance with the protocol. Programs will be developed for individuals by each AEP at the CCU and reviewed by the AEP from the research team each week to ensure sessions from each condition are conducted within the scope of the intervention. This will include; terms of number of repetitions, progression, and any necessary adaptation for pre-existing musculoskeletal conditions if present.

**7.1.4 Strategies to enhance adherence**

Participants from each condition will be offered a 20 minute fortnightly health coaching session utilising evidence based motivational strategies such as self- monitoring, goal setting, developing an understanding the value of physical activity and building self-efficacy for exercise, that is usual practice for accredited exercise physiologists. Motivational strategies will be based on Self Efficacy Theory which has been utilised in previous exercise interventions for people with SMI (13). Motivational strategies are recommended to increase adherence to exercise interventions (8). Participants will be encouraged to play music of their choice whilst exercising to enhance pleasure, or to choose to watch youtube videos on the CCU laptop. Participants will also be able to choose whether they wish to engage in sessions individually or in small groups, and to choose preferred exercise equipment or type of resistance activities within an accepted range of available exercises to ensure personal preference and autonomy is maximised, despite randomisation to condition.

**7.1.5 Randomisation Procedure and blinding**

Participants will be randomised once written consent has been obtained and the baseline assessments have been completed.

Participants will be assigned a unique code that will be sent to an independent biostatistician for randomisation using a computer -generated sequence of numbers. Randomisation to either RT or MIIT condition, will occur in a 1:1 ratio, using block randomisation.

Once randomisation has occurred, participants will be notified of their group allocation by an independent staff member to ensure the research team remains blinded to allocation.

There will be no opportunity to change conditions once randomised, however if participants wish they may withdraw from the study and continue to exercise using the equipment and AEP at each CCU independently from the study. If withdrawal occurs, reasons for doing so will be recorded in the CRF. Following randomisation, participants will be asked whether they are happy with the condition they have been randomised to, and this will be recorded in the CRF.

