# Study Population

Forty participants (50) undergoing psychiatric rehabilitation will be recruited through three Metro South Addiction and Mental Health Service Community Care Units (Logan, Coorparoo, Bayside).

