## Sample Size and Power

This study will be conducted as an exploratory RCT with feasibility as the primary outcome. Based on recruiting an adequate sample to assess the feasibility of the study with the resources available (63) we aim to recruit 50 participants assuming approximately 25 participants will be assigned to each intervention arm, based on previous exercise research within this setting – we anticipate 20% drop outs per exercise condition (49).

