## Statistical Analysis

Data analyses will be conducted using SPSS Statistics 24, (SPSS Inc, Chicago, Illinois) for the primary outcomes. Continuous variables were summarized using means and standard deviations (SD) (or median and interquartile range for non-parametric data). All variables will be tested for normality using the Shapiro-wilks test, and visual inspection of Q-Q plots. Baseline demographic and clinical variables, participation and AE rates and mean aggregate acceptability scores will be compared between the two exercise groups using independent t-tests or Mann-Whitney U for non-parametric data. Chi square analysis for categorical data will be used to detect any baseline differences between the two exercise groups and for comparison of acceptability categories (strongly agree/agree versus other) per questionnaire item between the groups.

Baseline demographic and clinical variables will be compared between the 2 exercise groups using independent t tests (or Mann Whitney U tests if data non parametric) for continuous data and Chi2 square analysis for categorical data to detect any baseline differences between the 2 exercise groups. Baseline characteristics of those who complete >50% of the program will be compared to those who withdraw to identify characteristics of those who drop out.

To analyse the impact of the proposed exercise intervention on secondary outcomes, analyses will be performed on an intention-to-treat basis. Change from baseline in secondary outcomes at week 8 will be calculated as least squares (LS) means using a Linear Mixed Effects Model (LMM). Treatment group (RT or AIT) and time will be used as factors, with covariates established in previous similar research (age, gender, participation, and antipsychotic medication use),(García-Garcés et al., 2021b). Where group/time differences were detected, posthoc (Bonferroni) analyses will be carried out separately for the intervention and control group, with Cohen’s d estimate of effect sizes provided. LMM was performed using R (software version 4.04, 2024). All the statistical tests were two-tailed with the critical P value for significance set at?<?0.05.

For the RT group only, 12 RM strength will be assessed for normality and compared pre and post the intervention using paired samples t test.

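### No stratification by care unit is specified and the stated analyses leave unit out, at a modest cost in precision and chance balance

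*Protocol*

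**What the plan says.** - **Sites.** Participants "will be recruited through three Metro South Addiction and Mental Health Service Community Care Units" (Study Population). Sessions take place on site with each unit's own gym equipment (Section 7.1).
- **Allocation.** Randomisation "will occur in a 1:1 ratio, using block randomisation" (Section 7.1.5). An independent biostatistician holds the computer-generated sequence. The section gives no block size and no stratification factor, and does not say whether each unit has its own list.
- **Delivery.** For resistance training, the exercises "will be supervised by the AEP employed at each site" (Section 7.1.1). For aerobic training, "Participants will engage in a circuit style training supervised by the AEP at each site" (Section 7.1.2). "Programs will be developed for individuals by each AEP at the CCU" (Section 7.1.3), after one day of training and with weekly review by the research team's physiologist. Fortnightly coaching aimed at adherence is also offered (Section 7.1.4).
- **Analysis.** "Treatment group (RT or AIT) and time will be used as factors, with covariates established in previous similar research" (Statistical Analysis); the covariates listed are age, gender, participation and antipsychotic use. Participation and adverse event rates are compared between arms by t-test or Mann-Whitney test. The ANOVAs for exercise preference and for the SEES carry no unit term either.
- **Size.** "we aim to recruit 50 participants assuming approximately 25 participants will be assigned to each intervention arm", with 20% dropout expected in each arm (Sample Size and Power).

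**The concern.** Unit is the clearest structural factor in this trial. It fixes the equipment, the resident group and the person who writes programmes, supervises sessions and coaches for adherence. Attendance is one of the three feasibility criteria, and that person bears on it directly. The protocol is not merely silent on the analysis: it names the model terms and the two-group tests, and unit is in none of them.

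Two things are at stake. Variation between units stays in the residual error of a trial expecting about 40 completers. And in the single allocation that is realised, one arm may by chance draw more of its participants from a unit with better or worse attendance, with nothing in the analysis to correct for it.

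**Working it through.** **Planned size.** 2 × 25 = 50 recruited; 50 × (1 − 0.20) = 40 completers, 20 per arm. In reverse, 40/(1 − 0.20) = 50, which fits the forty named in Study Population if that figure means completers (an assumption). No effect size, standard deviation or power is stated, so there is no power figure to reproduce.

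**Inputs not in the protocol (assumed).** Unit sizes 17/17/17, 17/17/16 or 25/15/10; blocks of 4; units enrolling in random order; share of outcome variance due to unit, ρ, from 1% to 20%.

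**Chance imbalance.** Simulated allocation over three units:

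| Unit sizes | Event in at least one unit | Trial-wide blocks | Blocks within unit |
|---|---|---|---|
| 17/17/17 | 12:5 or worse | about 18% | not run |
| 17/17/16 | 65:35 or worse | about 22% | 0% |
| 25/15/10 | 65:35 or worse | about 44% | 0% |

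For 17/17/17, block sizes of 2, 4 and 6 all give about 18%.

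**Precision.** With arms balanced within units, removing the unit share leaves a residual variance of 1 − ρ, so omitting unit multiplies the standard error by 1/√(1 − ρ). Power is two-sided at 5% with 20 per arm, for assumed standardised differences of 0.5 and 0.8. Without unit it is 35% and 72%.

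| ρ | SE increase if unit omitted | Power with unit, 0.5 | Power with unit, 0.8 |
|---|---|---|---|
| 1% | 0.5% | 36% | 72% |
| 5% | 2.6% | 37% | 74% |
| 10% | 5.4% | 39% | 76% |
| 20% | 11.8% | 42% | 81% |

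For example, at ρ = 10%, 1/√0.90 = 1.054.

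**Is the formula too generous?** It ignores the 2 degrees of freedom and any imbalance between unit and arm. A simulation with 40 completers (14/13/13), no true effect and 10,000 runs per cell gives the standard deviation of the estimated arm difference:

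| ρ | Neither | Unit in model only | Stratified and unit in model |
|---|---|---|---|
| 5% | 0.3129 | 0.3195 | 0.3088 |
| 10% | 0.3087 | 0.3091 | 0.3003 |
| 20% | 0.3073 | 0.2902 | 0.2817 |

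Doing both lowers the spread by 1 − 0.3088/0.3129 = 1.3%, 1 − 0.3003/0.3087 = 2.7% and 1 − 0.2817/0.3073 = 8.3%. The model term alone gains nothing visible at 5% or 10%, and 1 − 0.2902/0.3073 = 5.6% at 20%. The formula is therefore an upper figure.

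**Bias and type I error.** In the same simulation, with neither stratification nor adjustment, the mean estimate is about 0 and the type I error is 4.9% to 5.1%. With stratification but unit omitted from the model, type I error falls to 4.7%, 4.3% and 3.7% for ρ of 5%, 10% and 20%. With both, it is 5.0% to 5.1%.

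**The case against.** - **The protocol does not rule stratification out.** List structure and block size often sit in a separate randomisation plan. This stands: the exact statement is that no stratification by unit is specified. The omission from the analysis does not rest on silence, because the model terms are listed.
- **A reader might infer that arm is confounded with unit, or that false positives increase.** Neither follows. Both arms run in every unit, so only chance imbalance is possible, and an unstratified, unadjusted analysis already allows for it in its standard error.
- **A reader might put the chance of a 12:5 split at 37%,** from 1 − (1 − 0.1435)³ with three independent coin-toss series of 17. That is simple randomisation. Blocking holds the overall arms level and brings the figure to about 18%. If units enrolled one after another, trial-wide blocks of 4 would bring it to 0%.
- **The gain may be small.** The unit share of variance is unknown, and training and weekly review should shrink it. Unit differences that are constant over time largely cancel in change from baseline. This stands for the secondary scales, but attendance and adverse events have no baseline to cancel against.
- **The primary outcome does not depend on it.** Recruitment above 50%, retention above 65% and attendance above 60% are judged against fixed thresholds. This also stands, and it limits the importance of the point.

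**Conclusion.** The point holds as a matter of precision and chance balance. No stratification by unit is specified, and the stated analyses omit unit although each unit's physiologist delivers both arms. The cost is an increase in standard error of at most about 0.5% to 12% over assumed unit shares of 1% to 20%, and a 22% to 44% chance of a 65:35 or worse split in some unit under assumed unit sizes, blocks of 4 and random enrolment order. The benefit would lie mainly in the attendance and adverse event comparisons, and in outcomes where units differ in change. The documents do not support a claim of bias by design, of inflated type I error, or of any threat to the feasibility thresholds. The change is worth making because it is cheap, not because the trial fails without it.

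**What to change.** 1. In Statistical Analysis, add unit as a fixed effect (2 degrees of freedom) to the mixed models. If baseline and week 8 are both modelled as responses, include unit by time as well (a further 2 degrees of freedom), because a unit main effect alone does not touch the contrast in change. Three units are too few for a reliable random effect.
2. Compare participation between arms with unit in the model, or with a rank test stratified by unit if the data are not normal.
3. In Section 7.1.5, state that the biostatistician's blocks are stratified by unit for any allocations still to be made. Do this together with step 1, since stratifying while omitting unit makes the tests conservative.
4. If enrolment is complete, make the analysis changes only, and expect little gain unless unit differences are substantial.

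The cost is a change to the randomisation list, a few incomplete blocks, and the degrees of freedom named above. Any change to the list during the trial should be documented with its date.

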# Adverse Events (AE) and Serious Adverse Events (SAE)

The investigator is responsible for the detection and documentation of events meeting the criteria and definition of an adverse event (AE) or a serious adverse event (SAE) as provided in this protocol. During the study, when there is a safety evaluation, the investigator or site staff will be responsible for detecting AEs and SAEs, as detailed in this section of the protocol

